## Participant timeline

### Treatment of subjects

#### Baseline examinations

At baseline, patients have undergone a polypectomy/EMR/ESD procedure for a T1 CRC with positive resection margins < 0.1 mm (R1) or indeterminate resection margins (Rx).

All original specimens will be centrally reviewed by one of two expert gastrointestinal pathologists at UMC Utrecht or Amsterdam UMC. Additional immunohistochemical staining will only be applied by our expert pathologists when there is suspicion of LVI on the H&E slides. The expert pathologist will review the slide within 5 working days. Afterwards, all slides will return to the original laboratories. In case of doubt on the presence of one or more histological high-risk features, the other expert pathologist will be consulted in order to reach consensus. In case no consensus can be reached, a third expert pathologist will be consulted. If the quality of the specimen does not allow reasonable determination of risk factors, they will be excluded from study participation.

Furthermore, a staging CT thorax-abdomen or X-thorax and CT abdomen is performed. In case of rectal location an additional magnetic resonance imaging (MRI) of the pelvis is performed. If the target lesion is visible on MRI, rectal location is defined as location distal from the sigmoid take off. If not visible on MRI, rectal location is defined as < 15 cm from anal verge on endoscopy. In addition, Carcinoembryonic Antigen (CEA) will be measured.

#### eFTR procedure

All participating endoscopists are trained in ex vivo porcine models and certified to perform eFTR procedures in the Netherlands. All endoscopists have extensive colonoscopy (≥ 1000 procedures) experience. To minimize the risk that outcomes of this study are influenced by a potential learning curve of the performing endoscopist, only endoscopists with sufficient experience (at least 10 personal eFTR procedures) can participate in this study.

Patients will receive standard bowel preparation, which includes oral intake of a split-dose PEG-solution and bisacodyl in accordance with the standard bowel preparation protocol of the participating center. Procedures will be performed in an out-patient setting under deep sedation with propofol or under conscious sedation by a combination of intravenous midazolam and fentanyl. Monotherapy with antiplatelet agents is continued, all other anticoagulants (double antiplatelet therapy or heparin, coumarins, warfarin, NOACs) are temporarily discontinued according to Dutch guideline. Prescription of procedural prophylactic antibiotic therapy is not advised, but is left at discretion of the performing endoscopist [25].

Before the start of the eFTR procedure the scar will be identified using both HD white light endoscopy (WLE) and narrow band imaging (NBI), blue laser imaging (BLI) or other digital chromoendoscopy. Endoscopists preferably take a minimum of three photos of the scar. The lateral margins of the target lesions can be marked by the use of coagulation with the marking probe (Ovesco Endoscopy, Tübingen, Germany) at the discretion of the endoscopist. Hereafter the colonoscope will be extracted from the patient and the FTRD will be mounted. The colonoscope with the mounted FTRD will be reintroduced and advanced to the scar. Then the scar/lesion will be resected as shown in Fig. 1. After collection of the specimen the FTRD will be demounted and the colonoscope will be re-introduced to inspect the resection site. Patients will be discharged according to local protocols. A normal diet will usually be started at postoperative day one (Fig. 2).

**Fig. 1 Fig1:**
[figure not shown]
Trial design

**Fig. 2 Fig2:**
[figure not shown]
Schematic illustration of the resection procedure (image used with permission from Ovesco Endoscopy AG from www.ovesco.com)

#### Histopathology handling

The resection specimen is stretched and pinned down on paraffin or cork before immersed into formalin. Histopathological analysis is performed by a gastrointestinal pathologist according to daily clinical practice. In case of presence of residual adenocarcinoma, deep and lateral resection margins will be assessed as well as all histological risk features (differentiation grade, depth of invasion, lymphovascular invasion and tumor budding (grade 2 or 3)).

In the eFTR specimen, the pathologist will assess the presence of reactive changes compatible with scar tissue in the specimen. Definite histopathological confirmation of complete scar resection is known to be difficult and might not always be possible. In case the pathologist is not able to histologically confirm complete scar resection, further treatment will be based on the macroscopic completeness of scar excision and patients will be followed according to protocol.

In addition, central review of all resected eFTR specimens will be performed after all patients are included in the study. The central review will be performed by two independent expert gastrointestinal pathologists. In this review, the presence of neoplasia, scar tissue and evaluation of completeness of excision regarding both neoplasia and scar will be evaluated by both expert pathologists. In cases without consensus, meetings will be organized to discuss discrepancies to reach consensus. In case no consensus can be reached, a third expert pathologist will be consulted.

H&E slides of all resected eFTR specimens will be collected from the different laboratories and digitalized at the Amsterdam UMC for review. After digitalizing the slides will return to the laboratories to ensure the completeness of pathology archives and optimal patient care.

In case of unexpected findings, the treating physician will be informed to discuss further treatment options with the patients after colorectal MDT discussion. Outcomes of these cases will be recorded in the study database.

### Follow-up

In case the specimen of eFTR contains residual cancer with high-risk features and/or incomplete eFTR resection (Rx/R1), the case should be discussed in a colorectal MDT board for further treatment options depending on histological and endoscopic findings. The same accounts for cases in which completion eFTR of the scar was technically impossible. The outcomes, subsequent treatment and further follow-up procedures of these cases will be recorded in the study database. In this prospective cohort study, the follow-up schedule will be in line with the Dutch Guidelines (in preparation).

For all detected local, nodal and/or distant tumor recurrences during follow-up, the outcomes and subsequent treatment will be recorded in the study database.

#### Endoscopic follow-up

Endoscopic surveillance for lesions located in the colon will be performed by yearly eFTR scar checks at 12, 24, 36, 48 and 60 months. In patients with T1 rectal cancer endoscopic surveillance of the eFTR scar will be performed every 6 months during the first two years followed by yearly scar checks at 36, 48 and 60 months. According to the Dutch guideline, scar checks will be combined with a full colonoscopy at 12 months and 48 months for CRC surveillance [27]. The eFTR scar will be thoroughly inspected with HD WLE and (digital) chromoendoscopy. Endoscopists preferably take a minimum of three photos of the scar. Scar biopsies (3 biopsies) will be taken at every surveillance, even from scars without signs of macroscopic recurrence. Endoscopic and histological findings compatible with granulation tissue or reactive changes can be left untreated. Recurrent/residual low-grade dysplastic adenoma or a sessile serrated lesion can be treated endoscopically with conventional treatment strategies. When high-grade dysplasia or submucosal invasive cancer is found, a tattoo (SPOT) should be placed followed by case discussion in a colorectal MDT.

Local luminal tumor recurrence is defined as the presence of any adenocarcinoma at the site of the eFTR scar at follow-up colonoscopy. Further treatment and follow-up will be planned individually depending on histology and further staging procedures in the participating centers.

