**Methods/design:**

In this nationwide, multicenter, prospective cohort study we aim to assess feasibility and oncological safety of completion eFTR following incomplete resection of low-risk T1 CRC. The primary endpoint is to assess the 2 and 5 year luminal local tumor recurrence rate. Secondary study endpoints are to assess feasibility, percentage of curative eFTR-resections, presence of scar tissue and/or complete scar excision at histopathology, safety of eFTR compared to surgery, 2 and 5 year nodal and/or distant tumor recurrence rate and 5-year disease-specific and overall-survival rate.

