### Outcomes

The primary outcome is to assess the 2- and 5- year local luminal tumor recurrence rate after scar resection by eFTR following a previous R1/Rx resection of low-risk T1 CRC.

The secondary outcomes are:to assess the feasibility of completion eFTR, defined as a macroscopic complete en bloc scar excision in > 80% of casesto assess the percentage of curative eFTR resections, defined as no residual cancer in the scar or in case any residual cancer a R0 resection for T1 CRC without high-risk features (poor differentiation, lymphovascular invasion and/or high-grade tumor budding (grade 2 or 3)to assess the presence of scar tissue and/or complete scar excision at histopathologyto assess the procedure-related adverse event rate and safety of eFTR compared to oncologic surgery in a historical patient-cohort for T1 CRCto assess the 2- and 5- year locoregional nodal and/or distant tumor recurrence rateto assess the 5-year disease-specific survival rate and overall survival rateto assess the 2- and 5-year luminal, nodal and distant tumor recurrence rate in patients not meeting our inclusion criteria, but who did undergo eFTR completion treatment followed by strict surveillance and are included in our observational arm

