#### Radiologic follow-up

For patients who have undergone an eFTR procedure for a tumor located in the colon, a standard protocol CT thorax-abdomen will be performed yearly at 12, 24, 36, 48 and 60 months to evaluate nodal and/or distant tumor recurrence. For rectal location, an MRI of the rectum will be performed every 6 months during the first 2 years after the eFTR procedure followed by yearly MRI scans at 36, 48 and 60 months. Results of our prospective eFTR registry showed the OTSC (clip) in situ after eFTR in only 10.9% after 4 months of follow-up. In the rare cases in which the clip could possibly hamper scar assessment or quality of radiologic follow-up, the OTSC can be removed with a dedicated cutting device. In case of suspected local, nodal and/or distant tumor recurrence the patient will be discussed in a multidisciplinary team meeting to discuss further treatment options according to local clinical practice, which is based on the Dutch CRC guideline [27]. Outcomes and subsequent treatment will be recorded in the study database.

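### Cancer at the eFTR site that is proven only outside colonoscopy counts in no recurrence endpoint, although the safety limit is stated for local recurrence in general

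*Protocol article*

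**What the plan says.** All references are to the protocol article.

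- **Primary outcome (Outcomes):** "The primary outcome is to assess the 2- and 5- year local luminal tumor recurrence rate after scar resection by eFTR".
- **Event definition (Endoscopic follow-up):** "Local luminal tumor recurrence is defined as the presence of any adenocarcinoma at the site of the eFTR scar at follow-up colonoscopy". No other section widens it.
- **Secondary recurrence outcome:** the abstract lists "2 and 5 year nodal and/or distant tumor recurrence rate and 5-year disease-specific and overall-survival rate". The Outcomes section adds the word locoregional before nodal. Read with the abstract, that word qualifies nodal disease and does not bring in non-nodal local disease.
- **Observational arm (Outcomes):** "2- and 5-year luminal, nodal and distant tumor recurrence rate in patients not meeting our inclusion criteria". This again has no category for local disease that is not luminal.
- **Imaging (Radiologic follow-up):** CT is done "to evaluate nodal and/or distant tumor recurrence". For rectal tumours "an MRI of the rectum will be performed every 6 months during the first 2 years after the eFTR procedure", then yearly. The section expects imaging to raise suspicion of local disease: "In case of suspected local, nodal and/or distant tumor recurrence the patient will be discussed in a multidisciplinary team meeting".
- **Scar findings (Endoscopic follow-up):** three biopsies are taken at every surveillance, including from scars that look normal. High-grade dysplasia or invasive cancer is referred to the MDT.
- **Recording (Follow-up; Radiologic follow-up):** outcomes and treatment of local, nodal and distant recurrences go into the database. Neither section says that they count towards an endpoint.
- **Safety criterion (Sample size):** the 6.6% limit and the 1/102 benchmark are described as local recurrence, with no colonoscopy condition. The failure rule then counts local luminal recurrences and is met at more than 5.

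**The concern.** The definition joins two things: what the event is (adenocarcinoma at the scar) and where it must be shown (at follow-up colonoscopy). The second condition removes some true local failures. One route follows from the protocol itself: high-grade dysplasia at the scar goes to the MDT, the patient is operated on, and adenocarcinoma is first proven in the specimen. Another is a local abnormality on MRI or CT that is proven by imaging-guided biopsy without ever being confirmed at colonoscopy.

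Such a case is not a primary event. Unless it also has nodal or distant disease, it is not a secondary recurrence event either. The survival endpoints would register it only through a death.

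The study's conclusion is about oncological safety, and its limit and benchmark refer to local recurrence. A narrower count is therefore set against a broader yardstick, and any difference between the two favours declaring safety.

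**Working it through.** **1. Which cases fall through**

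| Case at the eFTR site | Primary endpoint | Secondary recurrence endpoint |
|---|---|---|
| Found by scar biopsy at colonoscopy | Counted | – |
| Suspected on CT, MRI or CEA, then confirmed at any follow-up colonoscopy | Counted; the definition is not limited to scheduled visits | – |
| High-grade dysplasia at colonoscopy, adenocarcinoma first proven in the surgical specimen | Not counted as worded | Not counted unless nodal or distant |
| Proven only by imaging-guided biopsy, never at colonoscopy | Not counted as worded | Not counted unless nodal or distant |

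The gap is confined to the last two rows.

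**2. Reproducing the plan's figures**

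Inputs from Sample size: n = 137, limit 6.6%, assumed rate 2%, one-sided exact test at 0.05, drop-out 10%, benchmark 1/102.

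- Cut-off: the largest c with P(X ≤ c | 137, 0.066) ≤ 0.05. P(X ≤ 4) = 0.0481 and P(X ≤ 5) = 0.1051, so c = 4.
- Power: P(X ≤ 4 | 137, 0.02) = 0.859, against a stated 86%.
- Inflation: 137 / 0.90 = 152.2, rounded up to 153, as stated.
- Exact one-sided 95% upper limit for 1/102: 4.57%, against a stated 4.6%.
- Exact one-sided 95% upper limits at n = 137: 6.56% for 4 events (within 6.6%) and 7.52% for 5 events (beyond it).

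The figures reproduce. The exact test passes at no more than 4 events, whereas the written rule also passes at 5. That mismatch is a separate matter, so both cut-offs are carried below.

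**3. Effect of uncounted cases**

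Let m be the share of true local recurrences never confirmed at any colonoscopy. The documents do not give m, so the values are assumptions. The counted rate is 6.6% × (1 − m), and the chance of declaring safety is P(X ≤ c | 137, counted rate).

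| m (assumed) | Counted rate when the true rate is 6.6% | Declared safe, at most 4 events (exact test) | Declared safe, at most 5 events (written rule) |
|---|---|---|---|
| 0% | 6.60% | 4.8% | 10.5% |
| 5% | 6.27% | 6.4% | 13.5% |
| 10% | 5.94% | 8.5% | 17.1% |
| 20% | 5.28% | 14.6% | 26.5% |

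**The case against.** The strongest defence is that the endpoint is deliberately luminal. The word recurs in the abstract, objectives, outcomes, failure rule, analysis section and discussion, and colonoscopy with biopsy is a coherent way to ascertain luminal cancer. Counting bowel-wall disease by any route changes what is estimated. Three biopsies at every scar check, yearly in the colon and 6-monthly for two years in the rectum, leave limited room for disease to escape endoscopy. The remaining cases are recorded and could be reported.

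Much of this stands. A reader might infer that any local recurrence found by imaging is lost. The text does not support that: it asks for adenocarcinoma at a follow-up colonoscopy, not that colonoscopy be the first test to raise suspicion. For the same reason, the share first detected outside colonoscopy cannot be used as the share lost; only cases never confirmed at colonoscopy are lost. A reader might also infer that a fifth event fails the study. That is the exact test's boundary, not the written rule. Any fixed cut-off turns on one event, so this sensitivity is not peculiar to the definition.

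What the defence does not answer is the mismatch inside the document. If luminal is the intended scope, non-luminal local failure has no recurrence endpoint, while the limit, the benchmark and the safety conclusion are expressed as local recurrence. Recording a case is not the same as a rule that it counts.

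**Conclusion.** The point holds in a narrow form. Adenocarcinoma at the eFTR site that is never confirmed at colonoscopy, and is proven only in a surgical specimen or by imaging-guided biopsy, is counted in no recurrence endpoint. The bias runs towards declaring safety.

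Its size is unknown and probably small. An assumed unconfirmed share of 5% to 20% raises the chance of a false safety declaration at a true 6.6% by 1.6 to 9.8 percentage points under the exact test (4.8% to between 6.4% and 14.6%), and by 3.0 to 16.0 points under the written rule (10.5% to between 13.5% and 26.5%). These figures assume 137 evaluable patients, a simple binomial count and the stated shares. The documents do not show that such cases will occur with any particular frequency.

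**What to change.** Define the primary event as histologically confirmed adenocarcinoma at the eFTR site (mucosa or bowel wall) by any route during follow-up: colonoscopic biopsy, imaging-guided biopsy or surgical specimen. Report the colonoscopy-only count as a sensitivity analysis, so that the luminal reading remains available. Use the same term in the outcome, the safety limit and the failure rule.

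The cost is a change of wording. The protocol already provides for recording these recurrences, so the change needs no added visits and no larger sample. The downside is that the observed rate may be slightly higher.

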#### Radiologic follow-up

For patients who have undergone an eFTR procedure for a tumor located in the colon, a standard protocol CT thorax-abdomen will be performed yearly at 12, 24, 36, 48 and 60 months to evaluate nodal and/or distant tumor recurrence. For rectal location, an MRI of the rectum will be performed every 6 months during the first 2 years after the eFTR procedure followed by yearly MRI scans at 36, 48 and 60 months. Results of our prospective eFTR registry showed the OTSC (clip) in situ after eFTR in only 10.9% after 4 months of follow-up. In the rare cases in which the clip could possibly hamper scar assessment or quality of radiologic follow-up, the OTSC can be removed with a dedicated cutting device. In case of suspected local, nodal and/or distant tumor recurrence the patient will be discussed in a multidisciplinary team meeting to discuss further treatment options according to local clinical practice, which is based on the Dutch CRC guideline [27]. Outcomes and subsequent treatment will be recorded in the study database.

#### Other follow-up

Surveillance with Carcinoembryonic Antigen (CEA) detection in serum will be performed every 6 months for 5 years after the performed eFTR procedure.

#### Observational arm

Patients who will undergo a completion eFTR following a previous incomplete excised T1 CRC, despite being non eligible for study participation (after multidisciplinary team discussion), will be prospectively followed in our study database. Furthermore, treatment outcomes of all non-eligible patients (eg because of the presence of high-risk features or the indetermination of those) will be collected in case no eFTR is performed.

### Sample size

Up-to-date, literature is scarce with regard to local luminal recurrence rates after endoscopic incomplete resection of T1 CRC (R1/Rx resections) for low-risk T1 CRC. A recent study showed local recurrence rates of 4.5% (4/89) after full-thickness resections of incomplete resected presumed low-risk T1 CRC. However, in this study histologic reassessment was not performed before resection and retrospective histologic revision showed high-risk factors for LNM in 3 out of 4 local recurrences [41].

Another study observed a local recurrence rate of 1% (1/102) during almost four years of follow-up after minimally invasive transanal surgery [42]. Considering that literature is limited, the upper limit of its 95% one-sided confidence limit may extend to 4.6%. With already being frequently used in daily practice and considering that the follow-up duration in the current study will by five years (instead of four), we opt to qualify eFTR as unsafe if the upper 95% one-sided confidence limit of its related local recurrence rate after five years extends beyond 6.6%.

A single sample size of 137 patients will have at least 86% power to detect this non-inferiority limit of 6.6% using a one-sided exact test with a significance level of 0.05 for maximum actually observed local recurrence rates of 2% over five years (twice the possibly underestimated local recurrence rate over four years of 1% for minimally invasive surgical treatment). To correct for potential drop-out patients in whom the primary outcome cannot be assessed the sample size will be adjusted to 153 (potential drop-out rate of 10%). These drop-out cases are patients with indication for additional surgery when histopathology review reveals high-risk features (i.e. poor differentiation grade, lymphovascular invasion and/or high-grade tumor budding) for LNM or eFTR is technically impossible. If during 5 years of follow up, more than 5 local luminal recurrences are observed -which implies that the upper limit of the confidence interval will exceed the non-inferiority limit- our study fails to establish oncological safety for completion endoscopic full-thickness resection after previous incomplete resection of low-risk T1 CRC.

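### The Sample size section gives two conclusions for one primary result, 'unsafe' and safety not established; only the second follows when the upper limit exceeds 6.6%

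*Protocol article*

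**What the plan says.** All the relevant text is in the Sample size section of the protocol article.

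- **Design.** The power claim is "A single sample size of 137 patients will have at least 86% power" against a margin of 6.6%. The method is described as "using a one-sided exact test with a significance level of 0.05". The alternative is a set of "maximum actually observed local recurrence rates of 2% over five years".
- **First statement of the rule.** "we opt to qualify eFTR as unsafe if the upper 95% one-sided confidence limit of its related local recurrence rate after five years extends beyond" the margin of 6.6%.
- **Second statement of the rule.** The section closes with a count. If more than 5 luminal recurrences occur in five years, the upper limit is said to exceed the margin, and "our study fails to establish oncological safety for completion endoscopic full-thickness resection after previous incomplete resection of low-risk T1 CRC".

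Both statements describe the same event, an upper one-sided 95% limit above 6.6%. One concludes that the technique is unsafe. The other concludes that the study has not shown it to be safe.

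**The concern.** An upper limit above 6.6% means that a recurrence rate of 6.6% or more has not been ruled out. It does not show that the rate is that high. 'Safety not established' is therefore a correct description, while 'unsafe', in its ordinary sense, claims more than the test can deliver. The document does not say which wording governs.

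What is at stake is how a middling result is worded. The Dissemination plans section expects the findings to enter the Dutch guideline, so the pre-specified conclusion should match what the data can support. The test, its margin and its error rate are not affected by this point.

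**Working it through.** **Inputs (Sample size section).** n = 137 analysable; margin p0 = 6.6%; design rate p1 = 2%, read here as the assumed true five-year rate; one-sided exact test at 0.05; stated power at least 86%; reference result 1/102.

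**Step 1. Reproduce the plan's figures.** Let X be the number of recurrences, binomial with n = 137 and rate p, so P(X ≤ c | p) = Σ C(137,k) p^k (1−p)^(137−k) for k = 0 to c.

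| Safety declared if | Type I error, p = 6.6% | Power, p = 2% |
|---|---|---|
| X ≤ 4 | 0.0481 | 0.8588 |
| X ≤ 5 | 0.1051 | 0.9419 |

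The stated 86% power at level 0.05 is the X ≤ 4 row. The exact one-sided upper limit for 1/102 is 4.57%, which matches the 4.6% in the section, and 137/0.9 = 152.2 rounds up to the 153 to be enrolled. The design figures hold together, with success at 4 or fewer recurrences.

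**Step 2. What each count shows.** The exact (Clopper-Pearson) upper limit solves P(X ≤ x | pU) = 0.05. The lower limit solves P(X ≥ x | pL) = 0.05.

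| Recurrences of 137 | Observed | Lower limit | Upper limit | Against 6.6% |
|---|---|---|---|---|
| 4 | 2.9% | 1.00% | 6.56% | higher rates excluded |
| 5 | 3.6% | 1.45% | 7.52% | undecided |
| 6 | 4.4% | 1.92% | 8.46% | undecided |
| 14 | 10.2% | 6.28% | 15.51% | undecided |
| 15 | 10.9% | 6.87% | 16.36% | rate shown to exceed 6.6% |

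From 5 to 14 recurrences the limits contain 6.6%. At 5 and 6 recurrences they also contain 2%. The first statement of the rule calls every one of these results unsafe.

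The undecided range depends a little on the method: 5 to 13 with Wilson limits, 4 to 15 with exact two-sided 95% limits.

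**Step 3. How often the label would appear at the hoped-for rate.** At a true rate of 2%:

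- Confidence-limit statement, 5 or more events: 1 − 0.8588 = 0.141, or 14%.
- Printed count, 6 or more events: 1 − 0.9419 = 0.058, or 6%.
- 15 or more events: about 1 in 10 million. In practice, every 'unsafe' label at this rate would come from an undecided result.

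**Step 4. The two triggers differ at exactly 5 events.** The exact upper limit for 5/137 is 7.52%, and the Wilson limit is 7.31%. Both exceed 6.6%, yet 5 is not more than 5. Only the simple normal-approximation (Wald) limit, 6.28%, stays below the margin, and the section specifies an exact test.

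**The case against.** The best defence is that the authors stipulate a label and do not draw an inference. They say they opt for it, and in a single-arm oncological safety study it is legitimate to withhold acceptance of a new technique until safety is shown. On that reading, 'unsafe' is shorthand for 'not shown to be safe', and the closing sentence, which carries the operational count, says so correctly. This largely stands. It is why the point is minor, but it also supports the correction, because the section already contains the right wording.

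Several stronger readings are tempting, and the document does not support them:

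- *An inconclusive result would be reported as evidence of harm.* No section says this, and the closing sentence points the other way. Any effect of the label on later treatment choices is conjecture.
- *The rule is badly calibrated.* At true rates of 3% and 4%, 5 or more events occur with probability 39% and 64%. These are ordinary non-rejection probabilities above the design alternative of 2%. The 14% at 2% is the complement of the stated 86% power. Nor does the document call every true rate below 6.6% acceptable: the Objectives section hypothesises less than 2%.
- *The rule penalises a small sample.* The upper limit widens with fewer patients, as it does under any confidence-limit criterion. Enrolling 153 is meant to protect the 137.
- *A formal three-way rule is required.* The study has no stated aim of proving harm, and a one-sided test has two outcomes by design.

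**Conclusion.** Wrong as written, minor severity. One section gives two conclusions for the same primary-endpoint result, and 'unsafe' does not follow from it. With exact one-sided 95% limits and 137 analysable patients, 5 to 14 recurrences leave the 6.6% margin undecided (6 to 14 if the printed count is the trigger). At a true rate of 2% the label would be attached with probability 14% under the confidence-limit statement, and the count would be exceeded with probability 6%.

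These figures assume a binomial count with every analysed patient followed for five years. The conclusion about the wording does not depend on them: failing to exclude a rate never by itself shows that rate.

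The disagreement between the limit and the count at exactly 5 events is a separate inconsistency in the section. It weighs more than the label, because the type I error is 0.105 if 5 events pass and 0.048 if they do not.

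**What to change.** 1. In the Sample size section, replace the phrase that qualifies eFTR as unsafe with one that considers oncological safety not established. This brings it into line with the section's last sentence.
2. State that the five-year recurrence estimate will be reported with its confidence interval whatever the outcome.
3. Reconcile the printed count with the confidence limit. With the exact test, the 6.6% margin, level 0.05 and 86% power as stated, failure begins at 5 recurrences of 137, that is, more than 4.
4. Optional: if the investigators want to keep the word 'unsafe' for some result, tie it to a lower one-sided 95% limit above 6.6% (15 or more of 137 with exact limits).

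Items 1 and 2 are wording only. They need no extra patients or data, and the margin, the sample size and the confidence-limit criterion for declaring safety stay as they are. Item 3 changes one number in the text and restores agreement with the stated error rate and power.

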### Statistical methods for primary and secondary outcomes

For our primary analysis all performed eFTR procedures in patients in whom the primary outcome (luminal local tumor recurrence rate after scar resection) can be assessed will be included. Thus patients in whom the procedure could not be performed for technical reasons or needing additional surgery due to the presence of high-risk features following completion eFTR will not be included for primary analysis.

For secondary analysis regarding feasibility of completion eFTR all included eligible patients will be analysed irrespective of the received completion eFTR or performed additional surgery.

Descriptive statistics will be used to describe patient, colonoscopy and eFTR characteristics for primary and secondary outcomes. Variables will be reported as mean with standard deviation in case of continuous and normally distributed variables, as median with an interquartile range (IQR) in case of non-normally distributed continuous variables, and as percentages in case of count or categorical variables. will use logistic regression with baseline variables to identify predictors for a successful completion eFTR.

The confidence interval of the 5 year disease-specific survival rate and overall survival rate will be calculated. Kaplan–Meier analysis will be used to estimate survival over time.

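### The cut-off of more than 5 recurrences does not match the plan's own 6.6% limit at any attainable sample size; the stated 86% power belongs to a cut-off of 4 or fewer at 137 patients

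*Protocol article*

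**What the plan says.** All the design figures stand in the Sample size section of the protocol article.

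- Criterion, with the limit set at 6.6%: "we opt to qualify eFTR as unsafe if the upper 95% one-sided confidence limit of its related local recurrence rate after five years extends beyond".
- Test and power: "A single sample size of 137 patients will have at least 86% power to detect this non-inferiority limit of 6.6% using a one-sided exact test". The level is 0.05. The section describes the recurrence rate behind this power as follows: "for maximum actually observed local recurrence rates of 2% over five years".
- Enrolment: 137 is raised to 153 for a potential drop-out of 10%. Drop-outs are patients who need surgery for high-risk features and patients in whom eFTR is technically impossible.
- Count: "If during 5 years of follow up, more than 5 local luminal recurrences are observed", the study fails to establish oncological safety. The text adds that such a count implies an upper limit above the non-inferiority limit.

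The count carries no sample size. The section on statistical methods makes the denominator variable: "all performed eFTR procedures in patients in whom the primary outcome (luminal local tumor recurrence rate after scar resection) can be assessed will be included".

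**The concern.** The section contains two rules for the same verdict: a confidence limit against 6.6%, and a fixed number of recurrences presented as its equivalent. If they part company at the planned size, the same data can be read as safe under one and unsafe under the other.

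At a true rate of 2%, fewer than three recurrences are expected among 137 patients (137 × 0.02 = 2.7), so a difference of one event can decide the trial's main conclusion. The printed power also has to belong to the rule that will be applied. A power figure for one cut-off combined with a verdict on another describes neither.

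**Working it through.** **Inputs (Sample size section).** Margin p0 = 6.6%; assumed rate p1 = 2%, taken as the true five-year rate; one-sided exact binomial test at 0.05; 137 evaluable; 153 enrolled; drop-out 10%.

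**Formulas.** For n analysed and X recurrences, the exact (Clopper-Pearson) one-sided 95% upper limit for x events is the p that solves P(X ≤ x | n, p) = 0.05. It is 6.6% or less exactly when P(X ≤ x | n, 0.066) ≤ 0.05. The matching cut-off c(n) is the largest such x. Power is P(X ≤ c(n) | n, 0.02).

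**Step 1: reproduce the plan's figures.**
- Upper limit for 1/102: 4.57%, against the plan's 4.6%.
- At n = 137: P(X ≤ 4 | 0.066) = 4.81% and P(X ≤ 5 | 0.066) = 10.51%, so c = 4. Power = P(X ≤ 4 | 0.02) = 85.9%, which is the stated 86%.
- 137 / 0.9 = 152.2, rounded up to 153.

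The sample size and power are therefore right, and they rest on passing with 4 or fewer.

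**Step 2: test the printed count at n = 137.**

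| Rule for passing | Upper limit at the boundary | P(pass) at true 6.6% | P(pass) at true 2% |
|---|---|---|---|
| 4 or fewer | 6.56% | 4.8% | 85.9% |
| 5 or fewer (as printed) | 7.52% | 10.5% | 94.2% |

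**Step 3: look for a sample size that rescues a count of 5.** The upper limit for 5 events is 6.75% at n = 153, 6.62% at 156 and 6.58% at 157. A count of 5 first meets the limit at 157, above the 153 enrolled. With all 153 analysed, the 5-or-fewer rule still passes 5.7% of the time at a true 6.6%.

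**Step 4: matching count by number analysed.**

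| Patients analysed | Most recurrences with upper limit at or below 6.6% | Limits near the edges |
|---|---|---|
| 116 to 136 | 3 | 3/116 = 6.55%; 4/136 = 6.604% |
| 137 to 156 | 4 | 4/137 = 6.56%; 5/156 = 6.62% |
| 157 and above | 5 (first size) | 5/157 = 6.58% |

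**Step 5: power when the 6.6% limit decides at the analysed n (true rate 2%).**

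| n | c(n) | Power |
|---|---|---|
| 130 | 3 | 73.7% |
| 136 | 3 | 71.0% |
| 137 | 4 | 85.9% |
| 143 | 4 | 84.0% |
| 153 | 4 | 80.7% |

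**Step 6: average over drop-out.** The plan gives no distribution for drop-out. Assume that the number analysed is Binomial(153, 0.90), with mean 153 × 0.9 = 137.7. Then P(n < 137) = 36%, with mean power 72% there, and P(n ≥ 137) = 64%, with mean power 85%. Overall: 0.36 × 72% + 0.64 × 85% ≈ 80% (80.3% before rounding). With 5%, 12% and 15% drop-out the average is 83.2%, 76.8% and 74.7%.

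**The case against.** The strongest reply has four parts.

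- **The confidence-limit criterion is already stated, and the sentence on the count is literally true.** Six or more recurrences do push the upper limit above 6.6% (6/137 gives 8.46%, 6/153 gives 7.59%). A careful analyst would still compute the limit and fail the study at 5. This stands as far as it goes. But the count is offered as the point at which safety is not shown, it is the only one given, and a reader will take 5 as passing. Having the right criterion nearby does not remove a second one that conflicts with it.
- **The printed power is not wrong.** This stands. A reader might infer from the step pattern that the 86% is a miscalculation or holds only at exactly 137. The documents do not support that: the figure is tied to 137 evaluable patients, where it reproduces, and power stays at 84% or more from 137 to 143. Stating power at the target number and then inflating for drop-out is normal practice.
- **The 80% average is not a figure of the plan.** This also stands. It needs the binomial assumption and a count recomputed at each n. A fixed rule of 4 or fewer, averaged over the same distribution, has power 85.7% and false-safe rate 4.7%. Nor is it correct that no fixed count could serve: 4 or fewer agrees with the limit at every n from 137 to 153. It departs only below 137, slightly at 136 (6.604%) and more at 130 (6.90%).
- **A look-up by n can be left to the analysis plan.** True of the look-up alone. It does not excuse a printed count that contradicts the printed limit.

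**Conclusion.** The point holds as an internal contradiction. The printed count breaches the plan's own 6.6% limit at every number of patients the study can analyse: with 5 recurrences the upper limit is 7.52% at 137 and 6.75% at 153. Used as the decision rule at 137, it roughly doubles the nominal 5% risk of declaring safety at a true rate of 6.6%, to 10.5%. The 86% power is correct for 4 or fewer at 137 and does not describe the printed rule.

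The dependence of the matching count on n is a secondary matter. It follows from analysing only assessable patients, and it bites when fewer than 137 are analysed.

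The limits, counts and error rates at a given n follow from the plan's figures and the exact binomial method alone. The power figures also take 2% as the true rate. Only the 80% average and the 36% chance of falling below 137 rest on the added binomial assumption about drop-out.

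**What to change.** 1. In the Sample size section, let one rule decide: compute the exact one-sided 95% upper limit on the patients actually analysed, and conclude safety only if it is 6.6% or less.
2. Replace the cut-off of more than 5 by the matching look-up: at most 3 recurrences if 116 to 136 patients are analysed, at most 4 if 137 to 156.
3. Keep 86% as the power at 137 evaluable patients. Add that under this criterion power is 71% at 136, 81% to 86% for 137 to 153, and about 80% on average if drop-out is taken as binomial at 10%.

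The cost is a few sentences of wording and a less favourable power statement. Five recurrences would then count as failure at any attainable size. Enrolment does not change.
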